#### Sample size and power

The power analysis is based on a two-sided Fisher’s exact test to compare the proportions of death within or at 28 days between the PMX treatment and control groups. It is assumed that for the control arm of standard medical care alone approximately 35% subjects will die by day 28 after the enrollment. It is also hypothesized that there will be an approximately 15% improvement in 28-day mortality rate for subjects randomized who receive the standard medical care plus the PMX cartridge, as compared to those receiving the standard medical care alone. The overall significance level for the entire sequence of primary efficacy tests is assumed at 5% in a two-sided test. An interim analysis based upon safety only was conducted after 76 patients were enrolled in January 2013. No efficacy analysis was conducted. The data safety monitoring board (DSMB) noted no specific safety concerns at that time. There is one planned additional interim analysis approximately at the midpoint (that is, 180 subjects enrolled). Because of the planned interim analysis, the maximum sample size for the trial (that is, if the trial is not terminated by the interim analysis) is based on the final efficacy test to compare day 28 mortality rate between the two study arms at a significance level of 0.048 based on the method of O’Brien and Fleming
[28].

Assuming a sample size ratio of 1:1 between the two study arms, a sample of 180 subjects per study arm (that is, a total of 360 subjects for both arms) provides at least 80% statistical power to detect the hypothesized effect size (that is, 15% difference) from the final primary efficacy test. The statistical power with the proposed sample size will thus be more than 80% from the entire sequence of the planned primary efficacy analyses. These power analyses assume a 15% attrition rate from the randomized subjects of each study arm. Therefore, a minimum of 306 evaluable subjects are necessary to achieve at least 80% statistical power based on the hypothesized effect size.

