#### Interim analysis

An interim analysis will be performed by an unblinded statistician independent of the DSMB and the Sponsor after the first 180 subjects (that is, about 90 per study arm, or about 50% of the total planned evaluable subjects) complete their day 28 assessment. The interim analysis will only analyze the portion of the data through day 28 for subjects who have completed the day 28 assessment and is based on the final efficacy test to compare day 28 mortality rate between the two study arms at a significance level of 0.048.

The primary purpose of the interim analysis is to determine if the trial should be terminated early or the study protocol should be modified. The primary population for this interim analysis will be the intention to treat (ITT) population. Secondary analyses will examine the modified ITT population - that is, all patients who have at least one treatment application. The issues to be addressed by the interim analysis will include the possibility that: (a) the treatment is clearly effective so that it is unnecessary to continue to the planned termination point insofar as the primary efficacy endpoint is concerned, *P* value is less than 0.005; or (b) the treatment is so ineffective that continuation of the study would provide little or no chance of ever reaching statistical significance. In addition to the efficacy assessment, at the interim analysis the DSMB will review all serious adverse events and unanticipated serious device effects to evaluate if there are medically significant justifications due to excessive side effects or safety concerns to demand an early end to the trial or a modification of the intervention. The interim analysis will thus evaluate both safety and efficacy variables.

If the trial is not terminated based on the interim analysis, the results of the interim efficacy analysis may be used to revise sample size estimations, which will serve in planning the remaining part of the trial. An independent statistician will conduct the power analyses and sample size re-estimation.

If the trial is terminated as a result of the interim analysis (that is, *P* value < 0.005) or by the recommendations of the DSMB, the final efficacy and safety analyses will be performed using the entire data of follow-up to 12 months or until the last assessment for all subjects randomized prior to the study termination date.

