### Statistical analysis of results

Primary efficacy analyses will be conducted on the ITT population. The primary efficacy endpoint is the all-cause mortality rate of the subjects within 28 days after the initiation of the treatment perfusion or the sham perfusion. Let *P*_0_ and *P*_1_ be the proportion of death within 28 days for the arm of standard medical care alone and the arm of standard medical care plus the PMX cartridge, respectively. The primary efficacy analyses will test the null hypothesis of *H*_0_ : *P*_1_ = *P*_0_ against the two-sided alternative hypothesis of *H*_
*a*
_ : *P*_1_ ≠ *P*_0_. The test of these hypotheses will be carried out through Fisher’s exact test
[29]. A two sided 5% significance level will be assumed for the primary efficacy test. Similar analyses on the primary efficacy endpoint will also be conducted on the per protocol population.

In addition, a long-term follow-up of survival status at 90 days, 6 months and 12 months will be undertaken for the ITT population. This will entail a comparison of survival rates for ITT subjects at 90 days, 6 months and 12 months after assignment to either the treatment perfusion or the sham control perfusion group.

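### The final primary test is set at 0.048 in one section and at 5% in another, so a final P between 0.048 and 0.050 has no defined verdict

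*Protocol article*

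**What the plan says.** Four statements in the protocol article bear on the level of the primary test.

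- **Sample size and power, overall level:** "The overall significance level for the entire sequence of primary efficacy tests is assumed at 5% in a two-sided test".
- **Sample size and power, final test:** because of the planned interim, the maximum sample size rests on a final analysis with an O'Brien-Fleming adjustment: "to compare day 28 mortality rate between the two study arms at a significance level of 0.048 based on the method of".
- **Interim analysis:** the interim look at 180 subjects "is based on the final efficacy test to compare day 28 mortality rate between the two study arms at a significance level of 0.048". The next paragraph gives the condition for stopping for efficacy: it is "unnecessary to continue to the planned termination point insofar as the primary efficacy endpoint is concerned, *P* value is less than 0.005". The section's last paragraph repeats the 0.005 as the ground for early termination.
- **Statistical analysis of results:** for the same 28-day mortality endpoint, by Fisher's exact test in the ITT population, "A two sided 5% significance level will be assumed for the primary efficacy test".

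The look at 76 patients was for safety only, so there are two efficacy looks. Trial status reports that the second interim analysis led to a new total of 650 patients.

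**The concern.** The section that governs the analysis and the section that justifies the design set different thresholds for the same hypothesis test. The analysis section speaks of one primary efficacy test and does not say that its 5% is the overall level for two looks. A statistician working from that section alone would declare success at P < 0.05. One working from the power section would require P < 0.048.

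The interim section adds to the confusion because its description of the interim look carries the level of the final test, next to a stopping rule at a different level.

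This is a pivotal regulatory trial, and its success criterion has to be a single number fixed in advance. If the final P falls between the two levels, the choice of threshold would be made with the result in view.

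**Working it through.** **Inputs.** Overall two-sided level 0.05, final level 0.048, control mortality 35%, difference 15 points (35% versus 20%), 180 per arm randomized, 15% attrition, 306 evaluable (Sample size and power). Interim at 180 subjects with P < 0.005 (Interim analysis). Alternative final level 0.05 (Statistical analysis of results). New total 650 (Trial status).

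**Step 1: reproduce the design.** For two equal looks, the O'Brien-Fleming critical values are c√2 and c, with c chosen so that the chance of crossing at either look is 0.05. The two z-statistics have correlation √0.5. Solving gives c = 1.977, that is, two-sided levels of 0.0052 and 0.0480. The protocol's 0.005 and 0.048 are this pair.

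The continuity-corrected sample size at 0.048 for 35% versus 20% is 153 per arm (306), and 153/0.85 = 180 per arm (360). Fisher power at 153 per arm and 0.048 is 80.5%. The design arithmetic is sound.

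**Step 2: nominal overall error.** With interim level a₁, final level a₂ and information fraction t:

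overall error = 1 − Pr(|Z₁| < z₁ and |Z₂| < z₂), with correlation √t and zᵢ the two-sided critical value for aᵢ.

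| Interim, final | t = 180/360 = 0.50 | t = 180/306 = 0.588 | t = 180/650 = 0.277 |
|---|---|---|---|
| 0.005, 0.048 | 4.99% | 4.94% | 5.13% |
| 0.005, 0.05 | 5.19% | 5.13% | 5.32% |

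At half information, using 0.05 instead of 0.048 adds 5.19 − 4.99 = 0.20 points.

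**Step 3: the test actually specified.** Fisher's exact test is conservative. Exact enumeration of the two-stage design, with 90 per arm at the interim and 0.005 then 0.05, gives these overall errors at null event rates of 20%, 35% and 50%:

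- 153 per arm: 3.7%, 3.8%, 3.6%
- 180 per arm: 3.9%, 4.1%, 4.1%
- 325 per arm: 4.2%, 4.4%, 4.8% (treating 650 as if fixed in advance)

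None exceeds 5%. With 0.005 then 0.048, the figure at a 35% event rate and 180 per arm is 3.9%.

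**Step 4: can the verdict turn on it?** Yes, for tables such as these:

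- 180 per arm, 62 versus 44 deaths (34.4% versus 24.4%): Fisher P = 0.0491
- 180 per arm, 52 versus 35 deaths: P = 0.0485
- 325 per arm, 97 versus 74 deaths: P = 0.0498

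Each succeeds at 5% and fails at 0.048.

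**Step 5: the resized trial.** If all 650 count toward the final test, the interim took place at t = 0.277. The last column of the table shows that 0.005 then 0.048 no longer holds 5% nominally. Solving for the final level that gives 5% after a 0.005 look yields 0.0467, before any allowance for the resizing having been driven by interim data.

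**The case against.** The strongest defence is that the 5% in the analysis section restates the overall level already fixed in the power section, in an article that condenses a longer protocol. The sentence does not use the word final and does not withdraw 0.048. That reading is possible, and it is why this is an ambiguity rather than a proven error. It does not remove the problem: the sentence refers to a single test, whereas the power section uses the whole sequence of tests when it means the overall level.

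Two stronger readings are tempting, and the document supports neither.

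- **That the overall 5% is exceeded.** This is true only of nominal levels on the normal approximation, and then by about 0.2 points at half information. The protocol specifies Fisher's exact test, whose two-stage error stays below 5% in every case enumerated above.
- **That the interim could stop the trial at 0.048.** Such a rule would spend about 8.0% nominally with 0.048 at both looks, and about 8.2% with 0.048 then 0.05. But the interim section attaches 0.048 to the final test and gives the efficacy stopping rule twice as P < 0.005. The 0.048 there is misplaced wording and sets no competing boundary.

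It is also fair to say that the window is narrow and that sample size and power hardly depend on the choice.

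**Conclusion.** The inconsistency stands. The final primary test has two stated levels, 0.048 and 5%, and the interim section carries the final-test level in a sentence about the interim. The consequence is an undefined verdict for a final P between 0.048 and 0.050. It is not a demonstrated loss of type I error control.

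For the 360-patient design the intended pair is clear: 0.005 then 0.048 reproduces O'Brien-Fleming and spends 4.99% nominally. This assumes one efficacy look at half the information. It does not carry over unchanged to 650 patients, where the same pair spends 5.13% nominally if all 650 enter the final test.

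**What to change.** 1. In Statistical analysis of results, state that the final primary test uses a two-sided level of 0.048 within an overall two-sided 5% across the interim and final looks.
2. In Interim analysis, give P < 0.005 as the only interim efficacy level, and mention 0.048 only as the level of the final test.
3. Because the trial was resized to 650, recompute the final level for the information fraction at which the interim actually took place, and state how the data-driven resizing is allowed for. The new value then replaces 0.048 in both sections. It should be settled before the final data are unblinded.

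The cost is a few sentences and a slightly stricter final threshold. At 153 per arm, Fisher power for the final test falls from 80.9% at 0.05 to 80.5% at 0.048. The planned 306 evaluable and 360 randomized already assume 0.048, so the original sample size does not change.

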#### Safety and the data safety monitoring board

An external, independent DSMB was established. The DSMB acts in an advisory capacity to the Sponsor to monitor subject safety, including mortality, which is also the primary efficacy endpoint of the intervention. The DSMB comprises a group of individuals with a broad and varied base of pertinent expertise who will review the accumulating safety data on a quarterly basis. The DSMB consists of a microbiologist, a nephrologist, a critical care physician, a biostatistician, and an expert in clinical trial design. The meetings consist of an open session blinded report and include participation by the sponsor and their representatives from the clinical research organization trial operations team and a closed session of only DSMB members and one unblinded representative from the CRO. The closed session report of data tables and listings from the database is presented in a blinded manner. The DSMB has the right to ask for unblinding any portion of the closed session report if they deem it necessary. The DSMB will conduct an unblinded interim analysis of the safety data when half of the subjects have completed the first 28 days of the trial. The DSMB will also provide expert opinion on the clinical relevance of any safety findings, address any safety issues mentioned by the sponsor and, where applicable based on the safety data, advise the Sponsor as to the appropriateness of continuing the trial according to the protocol or modifying the protocol. The DSMB may terminate the trial if they deem it necessary for the protection of the safety of potential or current participants.

DSMB members are reimbursed for reasonable expenses related to attending meetings, such as travel costs, accommodations, and meals. Members are compensated for their time spent performing their responsibilities as members of the DSMB. No other payment or future consideration is provided. No formal relationship exists between the DSMB and any other committee involved in the EUPHRATES trial.

## Discussion

There are several unique features of the EUPHRATES trial compared to prior severe sepsis/septic shock studies. The trial does not include an assessment for features of the systemic inflammatory response syndrome as part of standard inclusion criteria. These criteria lack specificity and have been heavily criticized
[30]. As an alternative, EUPHRATES targets patients with persistent shock and endotoxemia - aligning the purported mechanism of the treatment effect in hemodynamic improvement and the treatment of the presumed mediator of the disease process.

EUPHRATES is the first clinical trial in septic shock that we are aware of, designed to specifically use a biomarker as enrollment criteria for a therapy directed against that biomarker. This “theragnostic” approach has already proven successful in disease areas such as cancer and offers the opportunity to move beyond the constraints of the syndrome-based definition of sepsis to biologically targeted therapy
[4,31]. However, this approach by definition will limit the application of this therapy to only a part of our existing patient population with septic shock and endotoxemia, making the need to search for both new markers and new therapies even more important for those patients who do not have endotoxemia. Nevertheless, the approach may be a better way to conduct sepsis trials using smaller numbers of patients with higher efficacy hurdles. In this trial, if one were to assume that all patients were to be enrolled based on meeting clinical criteria alone and that 50% of those patients enrolled were not likely to benefit from the treatment, a required efficacy hurdle of 7.5% would be needed or a trial of nearly 1,200 patients. The duration, cost and complexity of such a trial would likely be prohibitive.

Finally, EUPHRATES is the first trial of a hemoperfusion device to our knowledge that will be blinded. While blinding offers significant advantages in the overall strength of the study, the use of a “sham” perfusion event rather than true sham perfusion was chosen because sham perfusion was felt to be unethical and invasive
[32]. Blinding a trial of this nature where patients are unstable and constantly interacting with numerous health-care providers is challenging and it is our intention to study the overall strength of the blinding procedures at the end of this trial so that lessons may be applied to future trials of this nature. This will be done by tracking all unblindings that occur, who was unblinded and how the unblinding occurred.

Thus, EUPHRATES is a pivotal trial using PMX hemoperfusion in patients with septic shock and confirmed endotoxemia. While the results of recent sepsis trials have been disappointing, there are several unique features of EUPHRATES, including its theragnostic design, that we hope are a step forward in the design of clinical trials for this underserved patient population.

## Trial status

The trial, at the time of submission of this manuscript, has enrolled approximately 275 subjects with all anticipated centers activated and trained. The second interim analysis was in the first quarter of 2014. Outcomes included a positive recommendation to continue the trial, sample size recalculation to a new total size of 650 patients, and addition of an exclusion criteria for multiple organ dysfunction score ≤9.

## Abbreviations

C4: Cooper University Hospital clinical coordinating center; CRF: case report form; DSMB: data safety monitoring board; EAA: endotoxin activity assay; EUPHRATES: Evaluating the Use of Polymyxin B Hemoperfusion in a Randomized controlled trial of Adults Treated for Endotoxemia and Septic shock; FDA: Food and Drug Administration; ITT: intention to treat; LPS: lipopolysaccharide; PMX: Polymyxin B; PMX-DHP: Polymyxin B direct hemoperfusion; SSC: Surviving Sepsis Campaign; TLR: Toll-like receptor.
